## Abstract

**Objective::**

The present clinical study aims to describe protocol to evaluate the effects of vitamin D3 supplementation on the cardiovascular risk factors in a population of rotating shift workers.

**Design::**

A randomized, double-blind, placebo-controlled, parallel group clinical trial testing 2 oral dosages of cholecalciferol (14,000 IU and 28,000 IU per week) for 12 months.

**Setting::**

The primary outcome for evaluation is an 18% reduction in hypertriglyceridemia (≥150 mg/dL) between pre and postintervention measurements. Baseline characteristics of the study population will be summarized separately within each randomized group, and will use tests for continuous and categorical variables. For all tests, a *P* < .05 will be considered significant. The analysis of primary and secondary outcomes will use an intention-to-treat population and a per-protocol population. The primary and secondary outcomes will be compared separately between each treatment group and placebo, using binary logistic regression or regressão de Poisson for proportions (for binary outcomes) and using linear regression for differences in means (for continuous endpoints), with 95% confidence intervals.

**Participants::**

Rotating shift workers, adults aged between 18 and 60 years, with hypovitaminosis D and alterations in at least 1 of the following parameters: fasting glucose, high-density lipoprotein cholesterol, triglycerides, low-density lipoprotein cholesterol, blood pressure, and waist circumference.

**Conclusion::**

This clinical trial aims to contribute to the gap in knowledge about the potential, dose, and time of vitamin D supplementation to generate beneficial effects on triglycerides in a population at increased risk for hypertriglyceridemia and vitamin D deficiency.

## Introduction

1

Hypovitaminosis D has affected populations in different age groups around the world.^[1,2]^ In the United States, Canada, and Australia, mean serum levels of 20 to 30 ng/mL were found,^[2]^ and the prevalence of hypovitaminosis D (<30 ng/mL) in Brazil ranged from 5.7% to 52.9% in men older than 18 years.^[1]^ There are still controversies about the reference values of vitamin D [25(OH)D]; the Brazilian Society of Endocrinology and Metabolism^[1]^ and the Endocrine Society^[3]^ define sufficient levels as values ≥30 ng/mL, and the Institute of Medicine^[4]^ defines sufficient levels as values ≥20 ng/mL. The literature data on vitamin D status in occupational groups are still scarce. However, when analyzing vitamin D status according to occupational activity, it is observed that shift workers and night-shift workers have lower levels of vitamin D and higher prevalence of deficiency and insufficiency when compared to day workers.^[5,6]^

Shift workers have a higher prevalence of risk factors for cardiovascular diseases, such as increased glucose, increased blood pressure, altered lipid profiles, and obesity when compared to day-shift workers.^[7–9]^ Shift work leads to deregulation of the circadian cycle, which promotes metabolic changes such as deregulation of cortisol, leptin, ghrelin, and melatonin, which contribute to the development of these risk factors.^[7,10]^ In a previous study by our research group with rotating shift workers, Batista et al^[11]^ showed that workers with hypovitaminosis D (<30 ng/mL) had a 5.9 times greater chance of having altered low-density lipoprotein (LDL) cholesterol (≥160 mg/dL) and a 2.3 times greater chance of having altered triglycerides (≥150 mg/dL) in relation to workers with sufficient levels of vitamin D.

Cross-sectional studies of several age groups suggest that hypovitaminosis D is associated with cardiovascular disease and risk factors, isolated or clustered, such as metabolic syndrome, waist circumference, body mass index (BMI), fasting glucose, blood pressure, total cholesterol, high-density lipoprotein (HDL) cholesterol, LDL cholesterol, and triglycerides.^[12–16]^ It is not yet clear whether there is a cause–effect relationship. There are few randomized clinical trials and with inconsistent results to provide an evidence on the benefit of vitamin D in reducing the risk of extraskeletal diseases, and most of those studies have been done in postmenopausal women^[17,18]^ (above 50 years), with normal sleep–wake rhythms. Thus, there are no data in the literature on the effects of vitamin D replacement in adult men (<60 years) who work in shifts.

Considering that there is still no consensus on the dose and time required for vitamin D replacement to generate beneficial effects in the cardiovascular profile, this clinical study aims to describe protocol to evaluate the effects of vitamin D3 supplementation at doses of 14,000 IU and 28,000 IU weekly for 12 months on the cardiovascular risk factors in a population of rotating shift workers. The hypothesis of the present study is that there will be an 18% reduction in hypertriglyceridemia (≥150 mg/dL) between pre and postintervention measurements in adult males with work activity that breaks the usual circadian cycle.

## Methods

2

### Trial design

2.1

A randomized, double-blind, placebo-controlled, parallel group clinical trial testing 2 oral dosages of cholecalciferol (14,000 IU and 28,000 IU) per week for 12 months with a 1:1:1 allocation ratio. This study will demonstrate the efficacy of supplementation with both doses of vitamin D in reducing hypertriglyceridemia.

### Participants

2.2

The study participants consisted of rotating shift workers from 5 units of a Brazilian iron ore mining company; all were adults aged between 18 and 60 years. The company's rotating shift schedule is 6 hours of work, followed by 12 hours of rest. All participants work 4 shifts on the following schedule: 7 PM to 1 AM, 1 PM to 7 PM, 7 AM to 1 PM, and 1 AM to 7 AM. After completing the 4-shift weekly cycle, they have a day off. The interviews and blood sample collection will occur in the workplaces.

The inclusion criteria are as follows:

25(OH)D levels <30 ng/mL (75 nmol/L)^[1]^With at least 1 of these parameters:Fasting glucose ≥100 mg/dL (5.55 mmol/L)^[19]^; HDL cholesterol <50 mg/dL (1.29 mmol/L) for women and <40 mg/dL (1.04 mmol/L) for men^[19]^;Triglycerides ≥150 mg/dL (3.88 mmol/L)^[19]^;LDL cholesterol ≥130 mg/dL (3.36 mmol/L)^[20]^;Blood pressure systolic ≥130 mm Hg or diastolic ≥85 mm Hg^[19]^;Waist circumference ≥80 cm for women and ≥90 cm for men.^[19]^

Subjects are excluded with evidence as following: malabsorption syndrome, kidney, liver, or thyroid diseases; specific drug use (anticonvulsants, corticosteroids, hormones, or vitamin and mineral supplements); or altered levels of serum creatinine, parathyroid hormone (PTH), serum calcium, or albumin. Among women, current breast feeding or pregnancy are also considered exclusion criteria.

After each visit (every 4 months), the follow-up will be interrupted if subjects evidence 25(OH)D >50 ng/mL (or 159 nmol/L) associated with altered serum calcium levels (>11 mg/dL) and with confirmation of a second test with altered serum calcium (>11 mg/dL) and PTH (<10 pg/mL) levels or evidence of vitamin D intoxication symptoms (dizziness, headache, nausea, rash, urticaria, weakness, numbness, and constipation); recent diagnosis of malabsorption syndrome, kidney, liver, or thyroid diseases; specific drug use (anticonvulsants, corticosteroids, hormones, or vitamin and mineral supplements); or participant request. In cases of interrupted due to intoxication, the code will be broken to clarify the diagnosis, only by the code keeper.

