### Safety

2.5

The 25(OH)D used in this trial already exists in the market, which has safety and quality. It was decided to 2 doses of vitamin D: 14,000 IU and 28,000 IU per week. The first one corresponds to maintenance therapy (1500 to 2000 IU per day) for replacement adult population at risk for hypovitaminosis D, in accordance with the Brazilian Society of Endocrinology and Metabolism^[1]^ and Endocrine Society.^[3]^ The second is double of maintenance therapy. It was decided to use this low dose to verify if the maintenance therapy is able to reduce hypertriglyceridemia, and double dose in order to increase the probability of generating a significant difference in the vitamin D status between the treatment groups and placebo. The clinical trial lasts for 12 months due to the seasonality of the incidence of ultraviolet radiation.^[21]^ In addition, vitamin D has endogenous synthesis via exposure to the sun and can be stored in adipose tissue,^[3]^ factors that make the placebo group necessary.

The risk of intoxication should be considered, but this condition is rare and caused by the intake of extremely high doses of vitamin D for long periods. The clinical symptoms of intoxication are characterized by hypercalcemia, hyperphosphatemia, suppression of PTH levels which can lead to nephrocalcinosis, and soft tissues calcification, especially blood vessels, in addition to fatigue, weight loss, anorexia, and impairment of renal function.^[1,3]^ The safe value of serum vitamin D levels suggested to avoid hypercalcemia is less than 150 ng/mL.^[3]^

Safety evidence for 25(OH)D supplementation has been reported by the Endocrine Society^[3]^ and by others authors, who did not observe serious adverse events. In a randomized trial, vitamin D supplementation with 6000 IU daily for 3 months, after 3000 IU daily for more 3 months and 2200 IU daily for more 3 months, was not associated with any adverse events or hypercalcemia during all 9 months of the study.^[22]^ In the vitamin D, diet and activity study, 2000 IU of cholecalciferol daily were supplemented for 12 months, and 4 women reported light-headedness, severe headaches, nausea, rash/hives, weakness/numbness, and constipation.^[17]^

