Symptoms of vitamin D intoxication include dizziness, headache, nausea, rash, urticaria, weakness, numbness and constipation, hypercalcemia, hypercalciuria, and associated kidney stones. To minimize the risk of vitamin D supplementation, individuals with a diagnosis of renal, hepatic, or thyroid disease were excluded. As a safety precaution, participants with 25(OH)D >50 ng/mL (or 159 nmol/L) associated with altered serum calcium levels (>11 mg/dL) and confirmation of a second test with altered serum calcium (>11 mg/dL) and PTH (<10 pg/mL) levels or evidence of vitamin D intoxication symptoms (dizziness, headache, nausea, rash, urticaria, weakness, numbness, and constipation) are excluded from trial. Additionally, measures will be taken to record adverse events or reactions: by the follow-up questionnaire every 4 months or in spontaneously by the participant by telephone/message or email to the responsible team.

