## Discussion

4

This is the first clinical trial evaluating 12 months of vitamin D supplementation in rotating shift workers. Shift work schedules are those that occur irregularly or uncommonly in comparison to usual daytime work (7/8 AM–5/6 PM), and can be fixed or rotating, continuous or discontinuous, and include or not include a night shift.^[48]^ Shift workers correspond to 14.8% of the workforce, with 2.5% rotating shift workers.^[49]^ In the mining area, the proportion of workers in rotating shifts is higher, reaching 31.9%.^[49]^

The shift work schedule allows activities 24 hours a day and aims to meet the needs of services, industries, and leisure.^[48]^ However, this work schedule contributes to the desynchronization of the circadian cycle. The circadian cycles are biological rhythms that are synchronized with external stimuli in order to adapt the organism to the environment in which it lives, thus allowing corporal homeostasis. Among the environmental factors, luminosity is considered the main external stimulus that promotes the synchronization of endogenous rhythms.^[10]^ Nighttime activities contribute to the misalignment of the circadian cycle, which can lead to adverse health consequences. Studies have reported that shift workers are at an increased risk for obesity, diabetes, metabolic syndrome, and cardiovascular diseases, as well as for increased glucose, triglycerides, total cholesterol, blood pressure, waist circumference and BMI, and for decreased HDL cholesterol ^[7–10,50]^.

In addition, Sowah et al,^[5]^ in a systematic review with 71 articles and a total sample of 53,345 workers, found, in shift workers, approximately 80% hypovitaminosis D (≤20 ng/mL), a higher risk of developing vitamin D deficiency (RR: 1.27; 95% CI: 1.26–1.28) and a higher risk of developing vitamin D insufficiency (RR: 1.24; 95% CI: 1.16–1.32) when compared to other occupational groups. This study suggests that these workers are more vulnerable to hypovitaminosis D. In a previous study conducted by our research group, with 391 rotating shift workers, we observed a high prevalence (73%) of hypovitaminosis D (<30 ng/mL).^[11]^

Therefore, the present study aims to contribute knowledge about the role of the dose and time of vitamin D supplementation in generating beneficial effects on triglycerides in a population at increased risk for hypertriglyceridemia and hypovitaminosis D.

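### Safety interruption rule: the 25(OH)D cut-off of 50 ng/mL is given as 159 nmol/L, but by the protocol's own conversion it is 125 nmol/L

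*Protocol article*

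**What the plan says.** Section 2.2 (Participants) gives 25(OH)D in two units twice. The inclusion limit reads "25(OH)D levels <30 ng/mL (75 nmol/L"). The rule for stopping a participant's follow-up, applied after each four-monthly visit, reads "the follow-up will be interrupted if subjects evidence 25(OH)D >50 ng/mL (or 159 nmol/L) associated with altered serum calcium levels (>11 mg/dL"). It goes on to require "confirmation of a second test with altered serum calcium (>11 mg/dL) and PTH (<10 pg/mL) levels", or symptoms of intoxication.

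Section 2.5 (Safety) restates the rule as a precaution, again for "participants with 25(OH)D >50 ng/mL (or 159 nmol/L) associated with altered serum calcium levels (>11 mg/dL"). It carries the same 50 and 159 and the same further conditions.

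Elsewhere 25(OH)D levels appear in ng/mL alone. Examples are the sufficiency definition in the Introduction ("define sufficient levels as values ≥30 ng/mL"), the hypercalcemia level in section 2.5 ("The safe value of serum vitamin D levels suggested to avoid hypercalcemia is less than 150 ng/mL") and the review cited in the Discussion ("approximately 80% hypovitaminosis D (≤20 ng/mL"). The text gives 25(OH)D in nmol/L only three times: 75 once and 159 twice.

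**The concern.** The two pairs in section 2.2 concern the same analyte and the same units, so one conversion factor must fit both. It does not. The bracketed form offers 159 nmol/L as a restatement of 50 ng/mL, yet the two figures are different cut-offs.

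The figure belongs to a rule that acts on participants. Meeting the rule ends follow-up, and section 2.2 adds that the code is broken when the interruption is for intoxication. Someone who applied the nmol/L figure would treat a participant between the two cut-offs as below the limit, so the slip makes the rule more permissive than its ng/mL wording. The trial was still running when the article was written (section 4.1), so the rule was in use.

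**Working it through.** **Inputs**, all from the protocol article:

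- Inclusion limit (2.2): 30 ng/mL = 75 nmol/L
- Interruption limit (2.2, repeated in 2.5): 50 ng/mL = 159 nmol/L
- Level cited for avoiding hypercalcemia (2.5): 150 ng/mL

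**Step 1. Factor from each pair** (nmol/L divided by ng/mL)

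- Inclusion limit: 75 / 30 = 2.5
- Interruption limit: 159 / 50 = 3.18

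The stated 159 is reproduced only with 3.18. That factor would turn the inclusion limit into 30 × 3.18 = 95.4 nmol/L, not the printed 75.

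**Step 2. Convert at 2.5**

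- 50 ng/mL × 2.5 = 125 nmol/L
- 159 nmol/L / 2.5 = 63.6 ng/mL

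**Step 3. Could rounding explain it?** Let 75 stand for anything from 74.5 to 75.5.

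- Factor: 74.5 / 30 = 2.483 to 75.5 / 30 = 2.517
- 50 ng/mL: 124.2 to 125.8 nmol/L
- 159 nmol/L: 63.2 to 64.0 ng/mL

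Rounding does not bring the value near 159.

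**Step 4. Could another compound explain it?** This step uses molecular weights that the article does not give, so it is an assumption and the conclusion does not depend on it. Taking 1000 / molecular weight with 400.64, 412.65, 384.64 and 416.64 for 25(OH)D3, 25(OH)D2, vitamin D3 and 1,25(OH)2D3, 50 ng/mL becomes 124.8, 121.2, 130.0 and 120.0 nmol/L. None reaches 159.

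**Step 5. Size of the gap**

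- In nmol/L: 159 − 125 = 34, and 34 / 125 = 27.2%
- In ng/mL: 63.6 − 50 = 13.6, and 13.6 / 50 = 27.2%
- Against the cited 150 ng/mL: 50 / 150 = 33%, and 63.6 / 150 = 42%

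**The case against.** The best reply accepts the arithmetic and disputes that it matters.

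- **The operative limit is clear.** ng/mL comes first in both places, other 25(OH)D levels are in ng/mL only, and the calcium and PTH limits in the same rule have no SI value. Nothing in the text says that results are reported in nmol/L, and the table of biochemical methods (Table 3) is not shown. On this view the wrong figure is a gloss that nobody uses.
- **25(OH)D alone stops no one.** The biochemical route also needs calcium above 11 mg/dL, then a second test with raised calcium and PTH below 10 pg/mL. If symptoms are a separate trigger, that route is unaffected.
- **There is a wide margin.** Even 63.6 ng/mL is 42% of the 150 ng/mL cited in section 2.5.
- **It is one slip printed twice**, and the text does not prove which member of the pair was intended.

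Most of this stands, and it is why the point is minor. It does not make the figure right: a stated limit in a safety rule contradicts the conversion used in the same section. A misread digit in the extracted text is unlikely, because the same 159 appears in both sections. The last objection is also fair, so the fix should begin by confirming that 50 ng/mL is the intended limit.

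**Conclusion.** The concern holds as a minor correction. By the protocol's own factor, 50 ng/mL is 125 nmol/L, and the printed 159 nmol/L is 27% too high. The error could change a decision only if three things coincided: the nmol/L figure was applied, the participant's level lay between 50 and 63.6 ng/mL, and the other conditions of the rule were met. Sample size, alpha, power and the primary analysis are not affected.

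The conclusion that the pair is inconsistent needs only the 30 to 75 conversion in section 2.2. Naming 159 as the wrong member rests on one further assumption, that the leading ng/mL value is the intended limit. The consistent use of ng/mL elsewhere makes that very likely.

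**What to change.** Confirm that 50 ng/mL is the intended limit, then give its SI equivalent as 125 nmol/L in both section 2.2 and section 2.5. If the full protocol or any working document carries the same pair, correct it there too. If any follow-up result was judged in nmol/L, look again at those between 125 and 159 nmol/L.

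The cost is one figure changed in two places. The ng/mL limit, the other conditions of the rule and the analysis stay as they are.

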### Data collection

3.1

The screening was performed in a population of 686 rotating shift workers; all individuals were invited to a general health assessment. All data were collected at the company's clinic through face-to-face interviews with a structured questionnaire assessment and a blood draw. The team responsible was composed of nurses, biochemists, nutritionists, and students, who were trained to collect the data before the study.

Figure 1 demonstrates all measurements that were evaluated at the screening visit, follow-up visits, and at the end of the 12-month supplementation period. At the screening visit, we are evaluating socioeconomic status, pre-existing diseases, drug use, sun exposure, lifestyle profile, quality of life, cognition (Table 2), blood pressure, biochemical data (Table 3), and anthropometrics and body composition measurements (Table 4). The follow-up visits will occur every 4 months and the supplementation delivery will occur every 2 months (it was integrated with follow-up visits). The follow-up visit procedures include blood sample collection, waist circumference measurement, and questionnaire interview. The vitamin D and lipid profile levels were quantified. The follow-up questionnaire monitors a presence of vitamin D intoxication, disease symptoms, drugs use, vitamins and minerals supplements, disease presence, treatment and others interventions during the trial, and food consumption alteration. At the end of the 12-month supplementation period, a reassessment of the general state of health was performed (Fig. 1).

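### The individual toxicity stop does not say whether a listed symptom is enough on its own, and it gives its 25(OH)D limit as two different values

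*Protocol article*

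**What the plan says.** The rule appears twice in the protocol article. Section 2.2 (Participants) applies it after each four-monthly visit. It joins four laboratory conditions: 25(OH)D above 50 ng/mL, calcium above 11 mg/dL, a second calcium above 11 mg/dL, and low PTH. It then adds the symptom alternative: "PTH (<10 pg/mL) levels or evidence of vitamin D intoxication symptoms (dizziness, headache, nausea, rash, urticaria, weakness, numbness, and constipation"). The consequence there is that follow-up is interrupted. Where the interruption is due to intoxication, the code keeper alone breaks the code to clarify the diagnosis.

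Section 2.5 (Safety) repeats the string and ends with a different consequence: "levels or evidence of vitamin D intoxication symptoms (dizziness, headache, nausea, rash, urticaria, weakness, numbness, and constipation) are excluded from trial".

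Both sections give the nmol/L equivalent of the 25(OH)D limit as 159; section 2.2 reads "or 159 nmol/L) associated with altered serum calcium levels".

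Two other statements in section 2.5 bear on what counts as intoxication. One is biochemical: "The clinical symptoms of intoxication are characterized by hypercalcemia, hyperphosphatemia, suppression of PTH levels". The other mixes complaints and biochemistry: "Symptoms of vitamin D intoxication include dizziness, headache, nausea, rash, urticaria, weakness, numbness and constipation, hypercalcemia, hypercalciuria, and associated kidney stones".

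Symptoms are collected by questionnaire (section 3.1: "The follow-up questionnaire monitors a presence of vitamin D intoxication, disease symptoms, drugs use"). The four-monthly questionnaire is also an adverse-event route in section 2.5 ("measures will be taken to record adverse events or reactions"), alongside spontaneous reports by telephone, message or email. Section 3.2 limits the ITT population to participants with outcome data.

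**The concern.** A stopping rule has to give the same answer whoever applies it. Here one questionnaire answer, for example nausea in a participant with normal calcium, is a stop on one reading and only an adverse-event entry on another. The listed complaints are non-specific and can occur in any arm, including placebo.

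Three things are at stake:

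- Handling may be inconsistent between participants or visits.
- Some codes may be broken without laboratory support for intoxication.
- Stopped participants may be lost from the primary analysis, because a stop ends follow-up or removes the participant from the trial and the ITT set requires an outcome.

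Separately, a decision limit stated as two different values cannot be applied consistently.

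**Working it through.** **Grouping.** Write D = 25(OH)D above 50 ng/mL, C1 = calcium above 11 mg/dL, C2 = second calcium above 11 mg/dL, P = PTH below 10 pg/mL, S = evidence of a listed symptom. The printed string allows at least four groupings:

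1. (D and C1 and C2 and P) or S
2. D and C1 and [(C2 and P) or S]
3. D and [(C1 and C2 and P) or S]
4. D and C1 and C2 and (P or S)

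| Participant | 1 | 2 | 3 | 4 |
|---|---|---|---|---|
| All laboratory limbs, no symptom | stop | stop | stop | stop |
| Symptom only | stop | stay | stay | stay |
| D and symptom | stop | stay | stop | stay |
| D, C1 and symptom | stop | stop | stop | stay |
| C1, C2, P and symptom, but 25(OH)D of 48 ng/mL | stop | stay | stay | stay |

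All four agree when the laboratory picture is complete. They disagree when a symptom occurs without it. Groupings 1 and 2 differ exactly when S is present and D and C1 are not both present.

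**Does other text settle it?** The semicolons in section 2.2 only separate the intoxication item from the disease, drug-use and participant-request items. The sentence in section 2.5 has no list punctuation. The biochemical description of intoxication in section 2.5 fits the groupings that need laboratory support. The list that puts headache and nausea beside hypercalcemia fits grouping 1. Neither sentence is about the stop. Section 3.1 names vitamin D and lipids as quantified at follow-up. Whether follow-up calcium is scheduled may be in Figure 1 or Table 3, which are not shown.

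**How ordinary the symptoms are.** Section 2.5 reports from a cited trial at 2000 IU daily that "4 women reported light-headedness, severe headaches, nausea, rash/hives, weakness/numbness, and constipation". These correspond to the eight stop symptoms if light-headedness is read as dizziness and hives as urticaria. The low arm receives 14,000 / 7 = 2000 IU per day, and section 2.5 cites that trial as evidence of safety.

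**Threshold.** The entry criterion in section 2.2 sets 30 ng/mL = 75 nmol/L, a ratio of 75 / 30 = 2.5.

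- 50 ng/mL × 2.5 = 125 nmol/L, not 159.
- 159 / 2.5 = 63.6 ng/mL, not 50.

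A value between 125 and 159 nmol/L (50 to 63.6 ng/mL) is over the limit in one unit and under it in the other.

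**Scale, on assumed rates only.** Suppose 1%, 5% or 10% of the 362 enrolled (section 4.1) report a listed symptom without both D and C1, and each report is accepted as evidence of intoxication:

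- 362 × 0.01 = 3.6, about 4
- 362 × 0.05 = 18.1, about 18
- 362 × 0.10 = 36.2, about 36

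Grouping 1 would stop these participants and grouping 2 would stop none. At equal rates across arms, one third are on placebo: about 1, 6 and 12. For comparison, the loss allowance in section 2.6 is 3 × 106 = 318, and 318 × 1.10 = 349.8, rounded to 350, so 350 − 318 = 32 participants.

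**The case against.** A reader might infer that any headache, in any arm and at any calcium level, stops and unblinds a participant, and that the women in the cited trial would all have been stopped. The documents do not support this. The rule asks for evidence of symptoms of vitamin D intoxication, which leaves room for clinical attribution. The code is broken only when an interruption is due to intoxication, and only by the code keeper. The text never says that a symptom-only stop counts as such, or who is then told.

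Grouping 1 also has a case as the intended rule. By convention "and" binds before "or", the sentence has a parallel structure, and a cautious safety rule may be deliberate. This is arguable but not conclusive, given the biochemical description of intoxication in the same protocol.

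It would be wrong for a reviewer to impose grouping 2. It would keep on capsules a symptomatic participant with confirmed high calcium and low PTH whose 25(OH)D was 48 ng/mL. That is a safety trade-off for the investigators to make.

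It can also be said that this is a condensed article, that the rates above have no anchor in it, and that time is short: enrolment was in November 2016 for 52 weeks, and section 3.1 describes the end-of-supplementation reassessment in the past tense. The lack of an anchor stands, so no expected number is claimed. Condensation does not explain the ambiguity, since the rule is printed in full twice and is unresolved both times. Tenses in the article are mixed and section 4.1 says the trial is not concluded, so the timing point limits the remedy without removing it.

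**Conclusion.** The concern holds as a drafting fault with a practical consequence. The individual toxicity stop does not determine what happens to a participant who has a listed symptom without the laboratory picture. The participant may be stopped, possibly with the code broken, or may continue. How many are affected is unknown. The illustrative 4, 18 and 36 of 362 rest wholly on assumed shares of 1%, 5% and 10% and on every such report being accepted as evidence of intoxication. No effect on the primary result is shown.

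The unit error is certain from the protocol's own ratio: 159 should be 125 nmol/L if 50 ng/mL is the intended limit, as its position as the leading value in both sections suggests.

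The loss from the ITT set follows from the stated consequences of a stop together with the ITT definition. It is conditional: it does not occur if the month-12 triglyceride is collected anyway.

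**What to change.** 1. Correct 159 to 125 nmol/L in sections 2.2 and 2.5.
2. Have the investigators state the grouping they intend, in identical words in both sections. At minimum, a symptom alone should trigger a prompt calcium check, with a temporary capsule hold if they prefer caution. The code should be broken only when laboratory findings support intoxication or when knowing the allocation is needed for care.
3. On any toxicity stop, stop the capsules but keep the participant in follow-up, collect the month-12 triglyceride and analyse as randomised. This replaces both the interruption of follow-up and the exclusion from the trial.
4. Report which reading was applied to any stops already made.

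The cost is rewording in two sections, an occasional calcium assay (a new draw when the symptom is reported between visits), and one retained month-12 draw per stopped participant. Items 2 and 3 can govern only visits still to come. Item 4 is possible at any stage.
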